### Recruitment of patients, randomisation and consent

When a patient is admitted, the investigator will contact the on-line randomization centre in the Clinical Research Support Centre [a centre providing design, management and coordination services for clinical trials and other studies conducted within the Health and Personal Social Services in Northern Ireland and funded by the Research and Development Office, Northern Ireland]. The investigator will complete the screening form on-line and this will generate a screening number indicating whether the patient is randomized or excluded. The randomization centre will provide the investigator with the allocation to receive either intervention A or B. The investigator will then obtain the appropriate intervention for the patient, which will be stored on the ICU. A record of all patients not randomized, including the reason for not being recruited, will be maintained by the investigator.

As patients are at risk from immediate exposure to MRSA from admission to the ICU, the success of this study will be dependent on randomizing patients as soon as possible. Furthermore as patients will be critically ill, they will not have the capacity to be able to give or withhold informed consent. Delay in recruiting patients would mean a significant proportion of patients would be excluded. Therefore, as the intervention is low risk, we plan to randomize patients on admission and obtain prospective/retrospective consent from their legal representative as soon as possible. In addition, retrospective consent will be obtained from the patient as soon as they are competent. This approach has previously been adopted in trials in the critical care setting [19-21]. In line with The Medicines for Human Use (Clinical Trials) Regulations 2004 and to comply with the Research Governance Framework, consenting processes will be standardised, and reinforced via training prior to study start-up. The planned flow of patients through the study is illustrated in Figure 1.

**Figure 1 F1:**
[figure not shown]
Participant enrolment flow diagram.

### Withdrawal from the study and the intervention

Individual patients will remain in the study until one of the following study termination criteria is reached: death; pre-intervention MRSA screening test is subsequently found to be positive; unit discharge; or patient or legal representative decline consent or request withdrawal from the study. The intervention will be continued in participating patients until one of the following intervention termination criteria is reached: adverse effect arising from either preparation; discharge from the unit; or MRSA colonization.

### Outcome measures

The primary outcome measure is new MRSA colonization during the inpatient episode in ICU, as defined by detection of MRSA by conventional culture methods in screening swabs of nose and groin, or in clinical specimens processed by the laboratory in the course of normal clinical care. This outcome measure is important as infection is typically preceded by colonization. The definition of colonization is clearly defined and unambiguous and it has established resource implications.

The secondary outcome measures are as follows: cost savings per case of MRSA colonization avoided; incidence of MRSA bacteraemia in each group; consumption of glycopeptide antibiotics, linezolid, rifampicin and fusidic acid; maximum increase in sequential organ failure assessment (SOFA) scores during inpatient episode, with reference to admission baseline; and agreement between MRSA screening results obtained by conventional culture and the PCR assay under evaluation.

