### Participants and sample size

All patients admitted to the ICUs during the study period will be eligible for inclusion in the study except those patients who fulfil the following exclusion criteria: less than 18 years of age; known to be colonized with MRSA at the time of admission; on admission, are judged as unlikely to remain in the ICU for at least 48 hours; are recruited, but whose pre-intervention MRSA screening tests are subsequently found to be positive (by standard culture); consent declined; and have a known sensitivity to TTO.

The primary outcome measure is the difference in MRSA colonization between groups at ICU discharge. The incidence of MRSA colonization during ICU admission in the study population is 13% (data obtained from the feasibility study conducted in one of the ICUs). A sample size of 1080 subjects (540 in each group) will have 80% power at a two-tailed significance level of 0.05 to detect a clinically significant difference of at least 40% in efficacy between 5% TTO and standard body wash. As the study will be confined to ICU, with nursing staff administering the study treatment, compliance will be guaranteed. Given the intensive monitoring in ICU, we do not expect any loss to follow-up.

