### Data collection methods and assessments: TTO evaluation and PCR verification

Data will be collected in a standardized manner across both sites according to Standard Operating Procedures. In both sites, patients will have screening specimens for MRSA carriage (using conventional culture methods on nasal and groin samples) carried out as a component of routine care by the nurse responsible for their care on admission to the ICU. For pragmatic reasons, duplicate specimens for processing by the PCR assay will only be taken in the RICU in the Belfast HSCT. All specimens will be obtained prior to either intervention commencing and will consist of swabs from both the nose and groin of all patients. Patients whose admission screening is positive by either method will be removed from the study (see exclusion criteria).

To facilitate verification of the PCR assay in the Belfast HSCT study population, its results will be compared to the culture results. Where there is disagreement between the culture and PCR results both will be repeated. In instances when the culture is persistently positive but the PCR assay persistently negative, this will be recorded as a false-negative PCR result (assuming a true-positive culture result). In instances when the culture result is persistently negative but the PCR assay is persistently positive, this will be recorded as a true-positive PCR result (assuming a false-negative culture result). If either test is not consistently positive or negative, it will be recorded as equivocal.

The presence of established major risk-factors for MRSA will be recorded, so that each can be analyzed as a covariate. These are:

• Total number of antibiotic-days during the ICU episode [24-26].

• Age (blocked by 10-year intervals).

• Number of comorbidities

• Intravascular catheter-days (number of devices × number of days) [27,28].

• Length of ICU stay [28,29].

• Severity of illness on admission to ICU [29].

Several other MRSA risk factors exist, such as transfer from high prevalence clinical units, multiple prior hospitalizations and residence in a nursing home. However, if participants are culture-negative at the time of admission to ICU, then these factors are not significant and therefore will not be recorded.

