End-of-study screening specimens will be obtained from all participants on ICU discharge or death to identify those patients in whom MRSA acquisition has occurred during the inpatient episode. Additional information regarding MRSA acquisition as a result of MRSA detection in other clinical specimens taken as part of routine care in the ICU will also be recorded. The time of swab collection will be recorded.

Quantity of body wash will be determined by counting the number of bottles used. Antibiotic consumption will be retrieved from prospectively generated computerized patient records. Compliance and adverse effects will be monitored daily by incorporating a record of washing (including time of washes) and adverse events in standard nursing records.

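### The primary outcome has no start time and accepts specimens from sites not swabbed at baseline, so carriage missed by the admission screen can be scored as new colonization, even from a specimen taken before the first wash

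*Protocol article*

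**What the plan says.** **Outcome (Outcome measures).** The definition begins: "The primary outcome measure is new MRSA colonization during the inpatient episode in ICU, as defined by detection of MRSA by conventional culture methods", and the detection may be "in screening swabs of nose and groin, or in clinical specimens processed by the laboratory in the course of normal clinical care". No minimum time from admission or from the first wash is given. The only 48-hour rule, under Participants and sample size, concerns expected length of stay at entry.

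**Who is taken out (Participants and sample size).** Patients "known to be colonized with MRSA at the time of admission" are excluded, and so are those who "are recruited, but whose pre-intervention MRSA screening tests are subsequently found to be positive (by standard culture"). The withdrawal section likewise ends participation when the pre-intervention screen proves positive.

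**Baseline screen (Data collection methods and assessments).** "All specimens will be obtained prior to either intervention commencing and will consist of swabs from both the nose and groin of all patients". Belfast also takes duplicate swabs for PCR. This section removes a patient whose admission screen is positive by either method, whereas the exclusion criteria name standard culture only.

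**Missed carriage is foreseen.** When PCR stays positive and culture stays negative, "this will be recorded as a true-positive PCR result (assuming a false-negative culture result").

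**Timing data.** The same section states "The time of swab collection will be recorded" and has the time of each wash entered in the nursing records.

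**The concern.** The trial asks whether the wash prevents acquisition. *New* is made operational only by a negative nose and groin screen, yet the outcome accepts a culture from any site that yields a clinical specimen, from the first hour of the stay.

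Consider a patient with negative nose and groin swabs whose wound swab, tracheal aspirate, urine or blood, collected on arrival, later grows MRSA. The patient was not a known carrier and has no positive screening test, so stays in the study and becomes a primary outcome event. The specimen may predate the first wash.

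Events of this kind add about equally to both arms. They shrink the apparent relative reduction and lower power, in a trial sized at exactly 80% power with no allowance for loss.

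**Working it through.** **1. Does any passage stop the leak?**

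| Step | Sites or tests | Earliest time |
|---|---|---|
| Exclusion at entry | Carriage already known | Admission |
| Removal after recruitment | Nose and groin screen (culture; PCR also at Belfast) | Before first wash |
| Outcome event | Nose and groin screen, or any clinical specimen | None stated |

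The third row is wider than the second in site and has no start time. Nothing in the article treats a positive clinical specimen from arrival as a positive screen.

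**2. Reproduce the plan's figure.** Inputs from Participants and sample size: control rate 13%, 40% relative reduction (so 0.6 × 13% = 7.8%), 540 per group, two-sided 0.05.

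Power = Φ{[d√n − 1.96√(2p̄(1−p̄))] / √(p₁(1−p₁) + p₂(1−p₂))}, where d = p₁ − p₂ and p̄ is their mean.

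d√n = 0.052 × √540 = 1.208; 1.96 × 0.4317 = 0.846; (1.208 − 0.846)/0.4301 = 0.842; Φ(0.842) = 80.0%. The stated 1080 is reproduced.

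**3. Add missed carriage.** Assume that u percentage points of the 13% were present on arrival, missed by the screen and unaffected by the wash, and that the wash cuts the rest by 40%. The TTO rate is then u + 0.6(13 − u). The documents do not give u; 0.5 to 3 is an assumed range, and 1 point is about 5 patients per arm (0.01 × 540 = 5.4).

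For u = 1, the TTO rate is 1 + 0.6 × 12 = 8.2%. Then d√n = 0.048 × √540 = 1.115; 1.96 × 0.4353 = 0.853; (1.115 − 0.853)/0.4340 = 0.604; Φ(0.604) = 72.7%.

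**4. What could an early cut-off recover?** If it removed all of u, the rates would be (13 − u) and 0.6(13 − u). If it removed only half, because the other half is first found by a later specimen or the discharge swab, they would be (13 − u/2) and u/2 + 0.6(13 − u).

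| u | TTO rate as written | Apparent reduction | Power as written | Power, all u removed | Power, half removed |
|---|---|---|---|---|---|
| 0.5 | 8.0% | 38% | 76.5% | 78.3% | 77.4% |
| 1 | 8.2% | 37% | 72.7% | 76.4% | 74.5% |
| 2 | 8.6% | 34% | 64.4% | 72.4% | 68.2% |
| 3 | 9.0% | 31% | 55.6% | 67.9% | 61.1% |

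With half removed, the apparent reduction at u = 1, 2 and 3 is 38%, 37% and 35%, not 40%.

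**5. What could a 48-hour cut-off lose?** Suppose that it also discards 1 point of genuine early acquisition, and give it full credit for removing u. The control rate is then 13 − u − 1.

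- u = 1: 11.0% vs 6.6%, power 72.4%, against 72.7% with no cut-off.
- u = 0.5: 11.5% vs 6.9%, power 74.5%, against 76.5%.
- u = 0: 12.0% vs 7.2%, power 76.4%, against 80.0%.

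A 48-hour window can therefore cost as much power as it gains. A cut at the first wash does not have this problem, since an acquisition before any wash could not have been prevented by washing.

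**The case against.** The strongest case against is that the plan already separates new from existing carriage. Known carriers are excluded, every patient is swabbed before any wash, and positives are removed. At Belfast, 17 of the 27 study beds, the data collection section also removes PCR-positives, so some carriers missed by culture would go too. This stands, and it limits the point to carriage that the screen misses. A reader might infer that carriage on arrival is in general scored as new; the documents do not support that.

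Four further points stand in whole or in part.

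- Missed carriage exists before the wash can act, so randomization balances it on average. No bias towards either arm follows.
- It is too strong to say that the wash could never affect missed carriage. The article presents 5% TTO as able to decolonize skin, so missed skin carriage might be cleared before the discharge swab. The argument fits best for early clinical specimens, above all those collected before the first wash.
- The recruitment section stresses exposure from the moment of admission, so early acquisition is part of the target, and a 48-hour rule would discard some of it.
- Recording is promised for swab times. Aspirates, urine and blood are not swabs.

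It can also be said that an article may leave an attribution rule to the full protocol or analysis plan. Here, however, the article fixes the outcome itself and calls the definition unambiguous. As written, it counts a specimen collected before the first wash.

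**Conclusion.** The point holds in limited form. The outcome has no start time and reaches sites not checked at baseline, so screen-missed carriage can be counted as new, including from specimens that predate the intervention. The consequence is dilution and lost power, not bias towards one arm.

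The size is unknown. Under the stated assumptions (events equal in both arms, unaffected by the wash, a 40% reduction in the rest), 1 point of the 13% lowers power from 80% to about 73%, and 0.5 to 3 points give about 77% to 56%. These figures are illustrative only.

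Two stronger conclusions do not follow. The sample size is not miscalculated: 1080 is reproduced exactly from its stated inputs. Nor would a 48-hour window restore the 40% effect and the 80% power: missed carriage found later would still count, and the event rate falls. Whether that window belongs in the primary definition is a matter of judgement. Not counting specimens collected before the first wash is hard to argue against.

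**What to change.** 1. In Outcome measures, state that MRSA from a specimen collected before the first wash is colonization present on admission and not an outcome event. Apply the rule identically in both arms and keep the patient in the denominator.
2. Pre-specify a sensitivity analysis that counts only specimens collected more than 48 hours after ICU admission. Alternatively, make that window primary, with all positives as the sensitivity analysis.
3. Record collection time for every clinical specimen, not only swabs.
4. Reconcile the exclusion criteria (positive by standard culture) with the data collection section (removal if positive by either method). PCR is done only at Belfast, so the second rule would filter existing carriage differently at the two sites.

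The cost is a sentence in the outcome definition, one extra analysis and one added time field; wash times are already recorded. The 48-hour window has a real downside: it drops some genuine early acquisitions and lowers the event rate. That is why it is offered first as a sensitivity analysis.

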### Schedule for assessments

Table 1 demonstrates the schedule for assessments to be performed at given time periods. Data for the previous 24-hours will be collected between 8 am and 10 am. The baseline assessment serves two purposes – first to ensure that patients recruited to the trial meet the inclusion criteria, and second to obtain baseline measures. Trial specific data will be collected in a Case Report Form for source data verification.

**Table 1 T1:** Timing of assessments

	Baseline	Day 1 to *n*	Day *n *(ICU discharge)	Hospital discharge
Inclusion/exclusion criteria	*			
Demographics	*			
APACHE II score	*			
SOFA score	*	*	*	
TISS score		*	*	
Isolation	*	*	*	
Steroid use	*	*	*	
Antibiotic list	*	*	*	
Invasive devices list	*	*	*	
Colonisation data	*	*	*	
Infection data	*	*	*	
No. of cultures sent to laboratory	*	*	*	
Adverse events		*	*	
Whether neighbouring patient has MRSA		*	*	
Standard groin swab	*		*	
Standard nasal swab	*		*	
PCR groin swab (Belfast HSCT)	*			
PCR nasal swab (Belfast HSCT)	*			
Details of wash	*	*	*	
No of body wash bottles used		*	*	
Duration of ventilation			*	
ICU length of stay			*	
ICU survival			*	
Hospital length of stay				*
Hospital survival				*
Discharge location				*

APACHE II – Acute Physiological & Chronic Health Evaluation II; HSCT – Health and Social Care Trust; ICU – Intensive Care Unit; MRSA – Methicillin-resistant Staphylococcus aureus; PCR – Polymerase chain reaction; SOFA – Sequential Organ Failure Assessment; TISS – Therapeutic Intervention Scoring System;

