### Statistical analyses

#### Hypothesis 1: TTO evaluation

For continuously distributed outcomes, differences between groups will be tested using independent samples t-tests, analysis of variance (ANOVA) and analysis of covariance (ANCOVA) with transformations of variables to normality if appropriate, or non-parametric equivalents. Chi-square tests (or Fisher's Exact tests) will be used for categorical variables. Major risk-factors for MRSA will be analyzed as covariates. Efficacy of intervention will be analysed on an intention to treat basis. A P value of ≤ 0.05 will be considered significant. A single final analysis is planned at the end of the trial.

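### The anti-MRSA antibiotic outcome has no baseline reference, and the stated covariates leave out baseline use of these drugs although it is recorded

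*Protocol article*

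**What the plan says.** Under Outcome measures, the protocol article names "consumption of glycopeptide antibiotics, linezolid, rifampicin and fusidic acid" as a secondary outcome. It gives no unit, no time window and no reference to use at admission. The outcome listed next to it does have one: "maximum increase in sequential organ failure assessment (SOFA) scores during inpatient episode, with reference to admission baseline".

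On data, the section on data collection says "Antibiotic consumption will be retrieved from prospectively generated computerized patient records". Table 1 (Schedule for assessments) marks "Antibiotic list" at baseline, on each ICU day and at ICU discharge. The same section says "Data for the previous 24-hours will be collected between 8 am and 10 am".

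On analysis, Hypothesis 1 (TTO evaluation) offers, for continuous outcomes, t-tests, "analysis of variance (ANOVA) and analysis of covariance (ANCOVA) with transformations of variables to normality if appropriate", or non-parametric equivalents, and adds "Major risk-factors for MRSA will be analyzed as covariates". The risk factors are listed in the data collection section. The only antibiotic item there is "Total number of antibiotic-days during the ICU episode". Use of the four listed drugs or classes at admission is not on the list.

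Under Participants and sample size, known MRSA colonization is an exclusion, but current treatment with one of these drugs is not.

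**The concern.** A patient may arrive in the ICU already on a glycopeptide, linezolid, rifampicin or fusidic acid. That is plausible here, because the Belfast unit takes patients from regional specialty departments and from other hospitals, but the documents give no frequency. Whether such a course was started cannot depend on the wash. Its remaining days add patient-to-patient variation to total consumption that has nothing to do with allocation, and an unadjusted comparison carries all of it.

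The covariate set does not help and could harm. ICU-episode antibiotic-days are counted after randomisation and contain the days on the listed drugs, so they are partly the outcome itself. Adjusting for them can absorb some of any effect of the wash on those days.

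At stake is the precision of one secondary outcome. It matters somewhat because this outcome measures a downstream consequence of colonization.

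**Working it through.** **The plan's own figure.** The article states no figure for antibiotic consumption. Its one sample-size figure reproduces: 13% against 13% × 0.6 = 7.8%, two-sided 0.05, 80% power, pooled variance without continuity correction, gives 540 per group, 1080 in total, and power 80.0% at 540. It concerns the primary outcome only and is not affected.

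**Illustrative model (all rates assumed).**
- A share p of patients is on a listed drug at admission, with a mean of 5 further days.
- Independently, 20% start a new course with a mean of 7 days.
- Both durations follow gamma distributions with shape k. Shape 1 is exponential; shape 4 has a coefficient of variation of 50%.

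**Share of drug-days from running courses:** 5p / (5p + 0.2 × 7).
- p = 0.1: 0.5/1.9 = 26%
- p = 0.2: 1.0/2.4 = 42%
- p = 0.3: 1.5/2.9 = 52%

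**Variance explained by the yes/no baseline indicator.**
- Explained: 25 p(1 − p)
- Running courses: 25 p(1 + 1/k) − 25p²
- New courses: 0.2 × 49 × (1 + 1/k) − 1.4²
- R² = explained / (running + new)

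Worked for p = 0.1 and k = 1: explained 2.25; running 5.00 − 0.25 = 4.75; new 19.60 − 1.96 = 17.64; R² = 2.25/22.39 = 0.10. For p = 0.3 and k = 4: explained 5.25; running 9.375 − 2.25 = 7.125; new 12.25 − 1.96 = 10.29; R² = 5.25/17.415 = 0.30.

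| Shape k | R² at p = 0.1 / 0.2 / 0.3 | Equivalent extra patients, 1/(1 − R²) − 1 |
|---|---|---|
| 1 | 0.10 / 0.15 / 0.17 | 11% / 18% / 21% |
| 2 | 0.14 / 0.21 / 0.24 | 16% / 26% / 32% |
| 4 | 0.17 / 0.26 / 0.30 | 21% / 35% / 43% |

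With very skewed course lengths (k = 0.5), R² is only 0.06 to 0.11, or 7-12% more patients. If admission use is rare (p = 0.02 to 0.05), R² is 0.03 to 0.06 at k = 1 and 0.04 to 0.10 at k = 4.

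**In terms of power.** If the adjusted comparison had 80% power, the unadjusted one would have Φ((1.96 + 0.84)√(1 − R²) − 1.96). This is 76% at R² = 0.1, 71% at 0.2 and 65% at 0.3.

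**The overlapping covariate.** Write total ICU antibiotic-days as T = A + O, where A is days on the listed drugs and O is other antibiotic-days. Suppose the wash lowers A by δ and leaves O alone. The mean of T then also falls by δ. With a within-arm slope b of A on T, the difference adjusted for T is δ − bδ = δ(1 − b). Because A is part of T, b will usually be positive, and the adjusted difference is then too small. A baseline indicator cannot do this, since allocation cannot change it.

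**The case against.** The strongest reply is that this argues from silence. The article does not say that running courses are counted, nor that they are left out. It condenses a full protocol, and a counting rule or covariate list may stand there or in an analysis plan. ANCOVA is already allowed, so baseline adjustment is not ruled out. This stands as far as the missing counting rule goes: that alone would be article-level detail. It does not answer the covariate point. A covariate set is stated, and its one antibiotic item is an overlapping post-randomisation measure where a baseline one would serve. It is fair to add that the covariate sentence does not say which outcomes it applies to.

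A reader might infer more than the documents support:
- **That the wash cannot affect running courses at all.** It cannot affect their start. MRSA acquired in the ICU could still prolong them. For that reason, restricting the outcome to new courses is debatable as the main analysis, because it would discard such an effect.
- **That the baseline list would remove the noise.** Table 1 shows a list, with no dose or start date stated. Adjustment reduces the variance but does not eliminate it.
- **That the gain is 20-43% more patients.** That range needs course lengths with a coefficient of variation near 50%. Exponential lengths give 11-21%.
- **That the comparison is biased.** Randomisation balances admission use in expectation.
- **That the cost comparison must be restricted too.** Total use is the proper input to costs.

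The model also ignores length of stay, severity and comorbidities, which are listed covariates. The gain beyond them has not been shown and may be smaller.

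**Conclusion.** The point holds as a modest matter of precision. The outcome has no baseline reference, the stated covariates omit baseline use of the listed drugs, and the one antibiotic covariate named is unsuitable for this outcome. The size cannot be fixed from the documents. With an assumed 10-30% on a listed drug at admission, baseline use explains roughly 10-30% of the variance for course-length shapes 1 to 4. It explains less if lengths are more skewed or admission use is rare. The primary outcome and the sample size are untouched.

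**What to change.** Add a sentence or two to the analysis section:
- Keep total drug-days of the listed agents as the outcome.
- Adjust for being on any listed drug at baseline (yes/no), taken from the Table 1 baseline antibiotic list. If a rank test is used, stratify by the same indicator.
- State that the indicator refers to use before randomisation, because the morning collection looks back 24 hours and could otherwise pick up later prescriptions.
- Do not use ICU-episode antibiotic-days as a covariate for this outcome.

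Courses started after randomisation can be reported as a supportive analysis. The cost analysis keeps unrestricted totals. No new assessments and no extra patients are needed.

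### Admission SOFA is not named as a covariate for the SOFA-rise outcome; adjusting for it costs nothing and is likely to improve precision

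*Protocol article*

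**What the plan says.** All references are to the protocol article.

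- **Outcome measures** lists as a secondary outcome the "maximum increase in sequential organ failure assessment (SOFA) scores during inpatient episode, with reference to admission baseline". It is the only organ-failure measure among the secondary outcomes.
- **Hypothesis 1: TTO evaluation** says that for continuous outcomes "differences between groups will be tested using independent samples t-tests, analysis of variance (ANOVA) and analysis of covariance (ANCOVA", with transformation or non-parametric equivalents where suitable. On covariates it says: "Major risk-factors for MRSA will be analyzed as covariates".
- **Data collection methods and assessments** gives the source of that set: "The presence of established major risk-factors for MRSA will be recorded, so that each can be analyzed as a covariate". The six items are antibiotic-days, age, comorbidities, catheter-days, length of ICU stay, and "Severity of illness on admission to ICU". No instrument is attached to the last.
- **Table 1** schedules SOFA at baseline, daily, and at ICU discharge. It schedules the "APACHE II score" at baseline only.

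The article does not say which of the tests or covariates applies to the SOFA outcome.

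**The concern.** The covariate set was chosen because its members predict MRSA acquisition. The section that states it also governs an organ-failure score, and the set does not name that score's own baseline value.

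Subtracting the admission score is not the same as adjusting for it. Subtraction fixes the slope of maximum SOFA on admission SOFA at 1, whereas ANCOVA estimates it. If the true slope differs from 1, the rise stays correlated with the admission score and that variation remains in the comparison as noise. At stake are the width of the confidence interval and the power for one secondary outcome, with the necessary data already being collected.

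**Working it through.** **The plan's own figure.** The article gives "A sample size of 1080 subjects (540 in each group" and "80% power at a two-tailed significance level of 0.05". Taking 13% in the control group and a 40% relative reduction (13% × 0.6 = 7.8%), with pooled variance and no continuity correction:

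n = [1.960·√(2 × 0.104 × 0.896) + 0.842·√(0.13 × 0.87 + 0.078 × 0.922)]² / 0.052² ≈ 540 per arm.

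This reproduces, but it concerns the binary primary outcome. No power, SD or correlation is stated for SOFA.

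**Inputs for SOFA.** From the article: 540 per arm, two-sided 0.05. Assumed: r, the correlation of admission with maximum SOFA, and s, the ratio of the SD of maximum SOFA to that of admission SOFA. Variances are in units of the admission SD squared.

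**Formulas.**
- Variance of the unadjusted rise: s² + 1 − 2rs
- Residual variance after adjusting for admission SOFA: s²(1 − r²)
- Difference between the two: (1 − rs)², where rs is the slope of maximum on admission SOFA. The difference is never negative and vanishes when the slope is 1.
- Power with adjustment, where the rise has 80%: Φ(2.802/√ratio − 1.960), where ratio is adjusted over unadjusted variance. With s = 1 the ratio is (1 + r)/2.

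| s | r | Slope | Variance, rise | Variance, adjusted | Ratio | Power (against 80%) |
|---|---|---|---|---|---|---|
| 1 | 0.3 | 0.30 | 1.40 | 0.91 | 0.65 | 93.5% |
| 1 | 0.5 | 0.50 | 1.00 | 0.75 | 0.75 | 89.9% |
| 1 | 0.7 | 0.70 | 0.60 | 0.51 | 0.85 | 86.0% |
| 1 | 0.9 | 0.90 | 0.20 | 0.19 | 0.95 | 82.0% |
| 1.2 | 0.5 | 0.60 | 1.24 | 1.08 | 0.871 | 85.1% |
| 1.5 | 0.5 | 0.75 | 1.75 | 1.6875 | 0.964 | 81.4% |
| 1.5 | 0.7 | 1.05 | 1.15 | 1.1475 | 0.998 | 80.1% |

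These rows are illustrations, not bounds.

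**Detectable difference** at 80% power with s = 1 and r = 0.5:
- Unadjusted rise: 2.802·√(2 × 1.00/540) = 0.170 SD
- Adjusted: 2.802·√(2 × 0.75/540) = 0.148 SD

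**If APACHE II is already a covariate** (s = 1; the APACHE II correlations are also assumed), the starting point is the APACHE II-adjusted rise at 80% power:
- APACHE II correlates 0.5 to 0.7 with admission SOFA and relates to maximum SOFA only through it: for r = 0.5 to 0.7 the ratio is 0.80 to 0.917, and power is 87.9% down to 83.3%.
- APACHE II correlates 0.6 with admission and 0.4 with maximum SOFA: at r = 0.5 residual variance falls from 0.96 to 0.734 and power is 89.3%; at r = 0.7 power is 83.6%.

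**If the severity covariate is SOFA itself and enters the SOFA model**, the adjustment is already made and the gain is zero.

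**The case against.** The strongest objection is that the article fixes no SOFA model. It offers a general menu that already includes ANCOVA, it does not say the MRSA risk factors are the only covariates, and a condensed article may leave the model for one secondary outcome to a fuller document. The admission-severity covariate might be SOFA. The gain depends on quantities the article does not give and can be close to nil.

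Much of this stands. A reader might infer that the plan rules out admission SOFA, or that the comparison certainly loses precision. The text supports neither: the first is not stated, and the second fails when the slope is near 1 or when severity means SOFA and is in the model. A reader might also infer bias. Under randomisation the unadjusted rise is unbiased. A chance admission imbalance has a standard error of √(2/540) = 0.061 SD with 540 per arm, and the confidence interval already reflects it.

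What does not stand is that nothing remains to be said. The article goes beyond silence: it states a covariate set, selected for a different outcome, and leaves this outcome's baseline unnamed. Listing ANCOVA does not cure that while the only covariates stated are MRSA risk factors. Table 1 shows APACHE II at baseline only and SOFA as a repeated measure, so APACHE II is the more natural reading of admission severity, though the article does not settle it.

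**Conclusion.** The point holds as a free improvement of minor weight. Naming admission SOFA as a covariate is likely to sharpen the SOFA comparison. Under the assumed values, power where the unadjusted rise has 80% runs from about 80% (SD ratio 1.5, r = 0.7) through about 90% (equal SDs, r = 0.5) to 93.5% (equal SDs, r = 0.3). The gain is smaller if APACHE II is already in the model. At 540 per arm, estimating one extra slope carries no material penalty.

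The conclusion rests on assumed correlations and SDs, and on reading admission severity as something other than SOFA. The 80% starting point is hypothetical, since the article claims no power for SOFA. The primary outcome and the sample size of 1080 are unaffected.

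**What to change.** In the analysis section for Hypothesis 1, add one sentence: the between-arm SOFA comparison is an ANCOVA with treatment as the factor and admission SOFA as a continuous covariate, reporting the adjusted mean difference with its 95% CI. Either maximum SOFA or maximum rise can be the response, because both give the same treatment estimate once admission SOFA is in the model. Keep the unadjusted t-test or a rank test as supportive. In the covariate list, name the instrument meant by admission severity.

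The cost is a sentence of wording and one clarification. Admission SOFA is already scheduled in Table 1, so no extra patients, visits or data items are needed. Naming the covariate in advance also removes a later choice of model in an open-label trial.
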